# The Effects of Acupoint Stimulation Combined With Transcutaneous Electrical Nerve Stimulation on Labor Pain: Protocol for a Stepped Wedge Cluster Randomized Controlled Trial

**DOI:** 10.2196/63050

**Published:** 2025-05-26

**Keywords:** labor pain, transcutaneous electric nerve stimulation, acupressure, complementary therapies, pain management, acupuncture points, medicine, Chinese traditional, pulsed electrotherapy, electrotherapy, nerve, pain, acupuncture, women, protocol, randomized controlled trial, childbirth, pregnancy, pregnant women, quantitative data, qualitative data

## Abstract

**Background:**

Pain experienced during childbirth can significantly impact the progress of labor and the well-being of both the mother and the fetus. Effective management of labor pain is a crucial component of childbirth care. Nonpharmacological methods of pain relief offer notable advantages over pharmacological approaches, including enhanced maternal and fetal safety, equitable access to health care, and greater availability. Among the nonpharmacological options, transcutaneous electrical nerve stimulation (TENS) and acupoint stimulation are two commonly used methods for alleviating pain during labor. However, the clinical efficacy of these methods remains inconsistent, which hinders the generation of high-quality evidence for clinical practice.

**Objective:**

This study aims to assess the effects of acupoint stimulation combined with TENS on labor pain, delivery outcomes, and childbirth experience for women undergoing a trial of labor.

**Methods:**

This is a 12-month stepped wedge cluster randomized trial to be conducted in 4 labor and delivery units (LDUs) at the Obstetrics and Gynecology Hospital of Fudan University. Each unit will implement 4 types of interventions: TENS, acupoint stimulation, TENS combined with acupoint stimulation, and a control group. We aim to recruit approximately 588 pregnant women. The project will be evaluated using both quantitative and qualitative data. Quantitative data will include visual analog scale (VAS) scores, the nonpharmacological to pharmacological pain management interval (NPI), the rate of epidural analgesia, and childbirth outcomes. Qualitative data will include interviews with the women and midwives.

**Results:**

The study commenced on April 1, 2023, and as of March 29, 2024, a total of 600 eligible participants have been enrolled, surpassing the initial target of 588. Data collection has been completed, including quantitative assessments of labor pain intensity, analgesic use, and childbirth outcomes, alongside qualitative interviews with participating women. Currently, data analysis is in progress, with preliminary findings anticipated to be available by March 2025. We hypothesize that TENS combined with acupoint stimulation will demonstrate greater efficacy in managing labor pain compared with standard care. This effect may be observed in key outcome measures, including the VAS score and enhanced maternal childbirth experience.

**Conclusions:**

This study protocol details the interventions of acupoint stimulation and TENS for women undergoing a trial of labor. We introduce a novel outcome indicator termed NPI, which monitors whether the application of nonpharmacological pain relief measures can delay or prevent the use of epidural analgesia. The integration of qualitative and quantitative methods will enrich the research on TENS and acupoint stimulation technology within the realm of nonpharmacological labor pain relief, providing high-quality evidence for the future establishment of industry standards and guidelines.

**Trial Registration:**

Chinese Clinical Trial Registry ChiCTR2300069705; https://tinyurl.com/2s3mkhr7

**International Registered Report Identifier (IRRID):**

DERR1-10.2196/63050

## Introduction

Childbirth pain is widely regarded as one of the most intense forms of pain, often cited by women as the most severe pain they have ever experienced [1]. Approximately 60% of primiparous women report experiencing severe or extremely severe labor pain [2], with 74.2% scoring 8 or higher on the pain perception scale [3]. The intensity of labor pain can lead to anxiety, fear, and tension, which in turn diminishes pain tolerance and exacerbates the cycle of pain. This can negatively affect the childbirth experience, potentially leading to prolonged labor, higher cesarean section rates, and increased risks for both mother and infant [4]. Therefore, effective pain relief strategies are essential for improving maternal health outcomes and the overall childbirth experience.

Pain relief during labor is typically categorized into two approaches: pharmacological and nonpharmacological [5]. Pharmacological methods, including epidural analgesia, nitrous oxide, and intravenous opioids, are generally more effective in managing pain [6]. However, they may have potential drawbacks, such as prolonged labor, dietary restrictions, the risk of intrapartum fever, higher cesarean section rates, and challenges with breastfeeding [7,8]. In contrast, nonpharmacological methods offer a range of alternatives that can reduce pain and anxiety with minimal risk to both the mother and fetus [9]. These approaches, which include transcutaneous electrical nerve stimulation (TENS), aromatherapy, water immersion, and massage, are recommended in clinical guidelines for enhancing the childbirth experience and reducing discomfort [10,11].

TENS and acupoint stimulation have both been extensively explored as nonpharmacological interventions for labor pain relief, each exhibiting distinct mechanisms of action. TENS involves the application of low-frequency electrical currents to stimulate the body’s pain-relief systems, primarily targeting the central nervous system to inhibit pain transmission [12]. Specifically, TENS at frequencies ranging from 2Hz to 100 Hz activates large-diameter Aβ fibers, which, at the dorsal horn level, inhibit incoming nociceptive signals transmitted through small-diameter, slow-conducting Aδ and C fibers that innervate spatially adjacent skin areas. This mechanism produces a pronounced analgesic effect in response to homotopic nociceptive stimulation [13]. TENS has been widely used for relieving chronic pain [14], postoperative pain [15], and cancer-related pain [16]. In the context of labor, several randomized controlled trials (RCTs) have found that TENS can reduce labor pain [17-19], shorten the active labor phase [19], and delay the need for pharmacological analgesia [18]. However, other studies have reported no significant effects on pain relief or labor satisfaction. Consequently, the efficacy of TENS remains inconclusive, with some studies indicating minimal effects on labor satisfaction and pain relief [1,20]. These conflicting results imply that TENS alone may not be adequate for consistent pain management during labor.

Acupoint stimulation, a traditional nonpharmacological method for pain relief rooted in traditional Chinese medicine (TCM), encompasses techniques such as auricular seed acupressure and acupoint massage. This practice is founded on the principle of promoting Qi and blood circulation to alleviate pain [21]. From a contemporary medical standpoint, acupoint stimulation is believed to function through the gate control theory, wherein massage or pressure inhibits nociceptive transmission [22]. In addition, it has been suggested that acupoint stimulation activates Mu opioid receptors, increases serum endorphin levels, and stimulates the release of adrenocorticotropic hormone, all of which contribute to pain relief [23]. Several studies have explored its application during labor, with findings indicating that acupressure can reduce pain during the first stage of labor [21] and that auriculotherapy can alleviate labor pain in primiparous women [24]. However, these studies frequently exhibit methodological limitations, such as small sample sizes and insufficient randomization, which hinder the ability to draw definitive conclusions regarding their effectiveness.

Although both TENS and acupoint stimulation have demonstrated analgesic effects, the existing evidence for nonpharmacological labor pain relief remains limited in strength and lacks standardized implementation protocols, which restricts its clinical applicability [25-27]. The combination of TENS and acupoint stimulation was selected for this study due to the complementary nature of their pain-relieving mechanisms. TENS primarily functions by modulating the nervous system to block pain signals, while acupoint stimulation enhances pain relief by promoting the body’s natural pain modulation processes, such as increasing endorphin release. Together, these approaches may provide synergistic benefits in alleviating labor pain and enhancing the overall childbirth experience. Furthermore, the combination of these two methods may optimize pain relief without increasing risks to the mother or fetus, thus offering a promising alternative to pharmacological interventions.

Based on these considerations, this study aims to evaluate the effects of acupoint stimulation combined with TENS on labor pain, delivery outcomes, and the overall childbirth experience for women undergoing a trial of labor. The primary hypothesis posits that this combination will lead to reduced labor pain, improved delivery outcomes, and a more positive childbirth experience for women. A stepped wedge cluster randomized controlled trial (SWCRCT) design is selected to ensure that all groups will ultimately receive the intervention, thereby promoting equity and adherence to ethical standards. This design also minimizes individual differences by using data from each group’s own participants as a control, while facilitating phased implementation, which effectively addresses resource and personnel feasibility [28].

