## Methods

### Trial Design

This 12-month exploratory SWCRCT will be conducted at the Obstetrics and Gynecology Hospital of Fudan University in Shanghai, China—a specialized tertiary hospital that manages approximately 10,000 births annually across its 2 campuses. The study involves 4 parallel groups, assigned in a 1:1 ratio, each receiving 1 of 4 interventions: TENS, acupoint stimulation, a combination of TENS and acupoint stimulation, or control measures. Randomization is performed at the cluster level using computer-generated sequences to determine the staggered initiation order of interventions across 4 labor and delivery units (LDUs; LDU1, LDU2, LDU3, and LDU4). Each LDU will be assigned to deliver a single intervention for a 3-month period, followed by a transition to the next phase according to the predetermined sequence. This design ensures that each 3-month cohort will comprise unique participants, eliminating crossover exposure to multiple interventions. Participants will be selected based on predefined criteria and confirmed for inclusion before the initiation of the interventions. Figure 1 shows the overall study flow. Recruitment began on April 1, 2023, and all interventions were completed by March 29, 2024, aligning with the 12-month study window. This protocol adheres to the SPIRIT (Standard Protocol Items: Recommendations for Interventional Trials) 2013 checklist [29].

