### Statistical Analysis

Data will be entered into the database after verification by 2 independent researchers. Quantitative data will be analyzed using SPSS 26.0 statistical software (IBM Corp), following an intention-to-treat (ITT) approach. Normally distributed continuous variables are presented as mean (SD), while non-normally distributed continuous variables are expressed as median (25th percentile-75th percentile). Categorical data are described using frequencies and percentages. Comparisons of normally distributed continuous variables were conducted using ANOVA or the Kruskal-Wallis test, while *t* tests were used for intergroup comparisons. A significance level of *P*<.05 is deemed statistically significant. Missing data will be addressed using multiple imputations.

Qualitative data will be analyzed using NVivo 14 software (Lumivero) through content analysis. Interview materials will be coded and categorized based on key themes derived from the interview guide. Perspectives on similar topics will be grouped and synthesized. Following coding, the software’s classification extraction function will be used to retrieve relevant content from all files under specific codes, allowing for comparison and linkage of different coded content, and identification of primary and secondary viewpoints based on frequency of occurrence for further analysis.

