### Comparison With Previous Work

This study builds on previous work by conducting a meta-analysis of 32 RCTs evaluating the use of TENS for labor pain relief [33]. The findings indicate that TENS can effectively reduce labor pain; however, the overall quality of the evidence was low, with significant heterogeneity across studies. This variability likely arises from individual differences among laboring women and inconsistencies in the implementation of TENS techniques.

Furthermore, previous studies have predominantly explored comparisons between nonpharmacological pain relief methods and pharmacological pain relief methods [1,36]. However, there is limited evidence on the sequential use of nonpharmacological interventions followed by pharmacological approaches, particularly in the context of delaying the administration of epidural analgesia.

Furthermore, several studies have demonstrated that nonpharmacological pain management can reduce the necessity for epidural analgesia [37] and that epidural analgesia is directly associated with an increased risk of intrapartum fever [34,35]. In light of this, we introduce a novel outcome indicator in this study: the NPI. Compared with the VAS, a subjective evaluation metric for assessing analgesic efficacy, the NPI provides an objective measure to evaluate how nonpharmacological pain management affects the use of epidural analgesia and the incidence of intrapartum fever. This study seeks to evaluate the effectiveness of TCM-based nonpharmacological pain relief methods in delaying and reducing the duration of epidural analgesia, thereby potentially lowering maternal fever rates and improving the quality of labor management.

We have also found that previous studies primarily focused on the effects of nonpharmacological pain relief measures during labor on quantitative health outcomes [19]. In contrast, the perceptions and experiences of women receiving labor pain management have been less thoroughly explored. This study aims to incorporate a mixed methods approach, supplementing the quantitative findings with experiential feedback from various stakeholders. This approach allows for a more comprehensive understanding of the effectiveness of TENS and acupoint stimulation in women undergoing a trial of labor.

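### Each labor unit, not each woman, is its own control in this design, and the named tests adjust for neither unit nor case mix

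*Protocol article*

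**What the plan says.** The design rationale in the Introduction states: "This design also minimizes individual differences by using data from each" group's own participants, who are to serve as the control. Trial Design describes what happens to the women: "This design ensures that each 3-month cohort will comprise unique participants, eliminating crossover exposure to multiple interventions". It also describes what happens to the units: "Each LDU will be assigned to deliver a single intervention for a 3-month period, followed by a transition to the next phase". Randomization and Allocation confirms that the LDU is allocated, not the woman, and Intervention limits each woman's exposure to one care episode.

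For the comparisons, Statistical Analysis says: "Comparisons of normally distributed continuous variables were conducted using ANOVA or the Kruskal-Wallis test", with t tests between groups. It names no LDU, period or participant term.

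Eligibility and Recruitment has women screened and consented on admission to the LDU and places no restriction on parity. Comparison With Previous Work, explaining heterogeneity among earlier TENS trials, says: "This variability likely arises from individual differences among laboring women", and gives inconsistent technique as a second cause.

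**The concern.** The rationale says the design deals with differences between individuals. No woman is observed under two conditions, so the design has no means of doing that. What recurs is the LDU, and using it as its own control deals only with features of a unit that stay constant over the year. The tests named in the article do not model even that comparison.

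This matters because of how women enter. A unit delivers one condition for three months, the sequence is disclosed to its midwives, and consent covers the pain relief method (Blinding). Trial Design confirms inclusion before the intervention starts, but that does not make recruitment blind to the unit's current condition. Parity, onset of labor and stage at admission can therefore differ between conditions by selection as well as by chance. With four LDUs, randomization of units gives limited protection. A reader who relies on the Introduction would think this had been taken care of.

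**Working it through.** **1. The plan's own figures.** Inputs from Sample Size: ICC 0.01, 117 per group, effect 0.7, alpha 0.05, power 0.8, 132 per group, 10% dropout.
- Design effect = 1 + (117 - 1) × 0.01 = 2.16, as stated.
- 132 / 0.9 = 146.7, rounded up to 147; 147 × 4 = 588, as stated.
- No SD is given. Before inflation, 132 / 2.16 = 61.1 per group. With a two-sided test (assumed), SD = √[61.1 × 0.7² / (2 × (1.960 + 0.842)²)] = 1.38. This implied SD is an assumption in step 3.
- No within-woman correlation enters any of these figures.

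**2. What recurs across conditions.**

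| | Under how many conditions | Source |
|---|---|---|
| LDU | several, in sequence | Trial Design; Abstract |
| Woman | one | Trial Design; Intervention |

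The only within-unit comparison available is within LDU, between different women.

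**3. What the LDU as its own control can remove.** At ICC 0.01, 1% of outcome variance lies between LDUs and 99% within them. For two groups of 147, before any clustering inflation:
- SE of the difference = 1.38 × √(2/147) = 0.161.
- With LDU variance removed = 1.38 × √(0.99 × 2/147) = 0.160.
- Reduction = 1 - √0.99 = 0.5%.

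**4. Chance imbalance in one prognostic factor.** Assumptions: 50% nulliparous; VAS gap by parity of 0.5 to 1.5 points.
- SD of the difference in nulliparous share = √(2 × 0.25/147) = 0.058, or 5.8 percentage points.
- Shift for one such SD = 0.058 × 0.5 = 0.03 to 0.058 × 1.5 = 0.09 VAS.
- Relative to 0.7: about 4% to 12%.
- This variation is part of the outcome SD, so the SE already reflects it.

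**5. What a large shift would require.** A 15-point imbalance is 0.15 / 0.058 = about 2.6 chance SDs. With the largest assumed gap it gives 0.15 × 1.5 = 0.225 VAS, or 32% of 0.7. Chance rarely produces that; it describes selection.

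**6. What covariates would gain.** If they explain a share R² of VAS variance (assumed 0.1 to 0.3), the SE is multiplied by √(1 - R²).
- R² = 0.1: factor 0.949, SE down 5%, equivalent to 147 / 0.9 = 163 women per group.
- R² = 0.2: factor 0.894, SE down 11%, equivalent to 147 / 0.8 = 184.
- R² = 0.3: factor 0.837, SE down 16%, equivalent to 147 / 0.7 = 210.

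**7. Are the named tests invalid for want of an LDU term?** In a simulation with an assumed layout (4 LDUs × 4 periods, each LDU delivering every condition once, 37 women per cell, ICC 0.01, no true effect, 4,000 runs), ANOVA rejected in 4.9% of runs when the whole ICC was a stable LDU effect. It rejected in 8.0% when half was LDU-by-period variation.

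**The case against.** The Introduction speaks of each group's own participants, just after saying that all groups eventually receive the intervention. Since LDUs are what move through the conditions, the natural reading is the usual stepped wedge argument that a cluster supplies its own control data. On that reading the uniqueness of the women contradicts nothing. The text also says minimizes, not removes. This stands: a reader might infer that the article claims each woman as her own control, and the wording does not support that. What remains is narrower: that argument covers differences between units, and the sentence credits it with covering differences between individuals.

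A reader might also infer that the sample size takes credit for within-woman control. It does not (step 1). Nor does the remark on individual differences identify case mix as a confounder here; it concerns earlier trials.

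Chance imbalance is not bias, and a shift of about a third of the target effect should not be quoted as a chance result (steps 4 and 5). The documents do not show that selection occurred. If every LDU delivers every condition in equal numbers, stable LDU effects also balance between conditions, so the missing LDU term does not by itself bias the contrast (step 7).

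Finally, a condensed article may leave covariates to an analysis plan that is not shown, and Blinding mentions a prespecified plan. That is fair for a detail left out. Here, though, the article itself names unadjusted tests, and that statement needs correcting whatever the plan contains.

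**Conclusion.** The point holds in limited form. The Introduction credits the design with dealing with individual differences, but only the LDU is its own control. At the protocol's ICC that accounts for 1% of outcome variance, and the named tests model neither LDU and period nor the women's characteristics. Differences between women are mainly noise, plus whatever selection arises from recruiting into a unit whose condition is known.

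Chance imbalance in parity is worth about 0.03-0.09 VAS, or 4-12% of 0.7, and is already in the SE. Anything much larger would need selection. The practical gain from adjustment is an SE about 5-16% smaller and some protection against measured case-mix imbalance. The nulliparous share, the VAS gap and R² are assumptions, because the documents give none of them. The comparison in step 3 also uses the implied SD of 1.38, although the 1% share depends only on the ICC.

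**What to change.** - **Introduction:** reword the rationale to say that each LDU serves as its own control, and drop the reference to individual differences.
- **Statistical Analysis:** for the primary outcome, replace the unadjusted tests with a model containing LDU and period terms and a short fixed list of pre-intervention covariates from the medical record: parity, spontaneous or induced onset, and cervical dilation at admission if recorded before the intervention.
- **Leave out the first VAS score.** Intervention and Table 1 start the techniques at the onset of contractions, and Outcome Measures starts the VAS at the onset of labor pain. The first score may therefore already be affected, and no intervention start is described for controls.
- **Timing:** lock the list before group labels are revealed to the statisticians, and declare that it was set after data collection.

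The cost is one reworded sentence, one model specification and a few record items. The article does not say that these items were captured at screening, so availability must be checked. The small downside is having to declare a list fixed after data collection. Adjustment corrects only measured imbalance.

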## Methods

### Trial Design

This 12-month exploratory SWCRCT will be conducted at the Obstetrics and Gynecology Hospital of Fudan University in Shanghai, China—a specialized tertiary hospital that manages approximately 10,000 births annually across its 2 campuses. The study involves 4 parallel groups, assigned in a 1:1 ratio, each receiving 1 of 4 interventions: TENS, acupoint stimulation, a combination of TENS and acupoint stimulation, or control measures. Randomization is performed at the cluster level using computer-generated sequences to determine the staggered initiation order of interventions across 4 labor and delivery units (LDUs; LDU1, LDU2, LDU3, and LDU4). Each LDU will be assigned to deliver a single intervention for a 3-month period, followed by a transition to the next phase according to the predetermined sequence. This design ensures that each 3-month cohort will comprise unique participants, eliminating crossover exposure to multiple interventions. Participants will be selected based on predefined criteria and confirmed for inclusion before the initiation of the interventions. Figure 1 shows the overall study flow. Recruitment began on April 1, 2023, and all interventions were completed by March 29, 2024, aligning with the 12-month study window. This protocol adheres to the SPIRIT (Standard Protocol Items: Recommendations for Interventional Trials) 2013 checklist [29].

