### Randomization and Allocation

This study uses a SWCRCT design, wherein the interventions are allocated at the cluster level, specifically based on the LDUs, rather than at the individual participant level. The randomization process is conducted by a researcher not involved in the intervention using a computer-generated random number list to determine the sequence of interventions across the 4 LDUs. The random allocation sequence is subsequently sealed in opaque envelopes, each corresponding to a specific LDU. This allocation sequence will be disclosed to the midwives in each cluster at the appropriate time. The midwives, trained to implement the intervention, will execute it according to the allocated sequence. This approach ensures allocation concealment and mitigates the risk of selection bias.

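### The trial is labelled a stepped wedge, but its schedule is a 4-period, 4-LDU cluster crossover, and the named tests carry no LDU or period term

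*Protocol article*

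**What the plan says.** The title, abstract, Introduction, Trial Design and Randomization sections all call the trial a stepped wedge cluster randomized trial. Four statements fix the schedule:

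- Abstract, Methods: "Each unit will implement 4 types of interventions". The list that follows is TENS, acupoint stimulation, the two combined, and control.
- Trial Design: "Each LDU will be assigned to deliver a single intervention for a 3-month period, followed by a transition to the next phase".
- Trial Design: "Recruitment began on April 1, 2023, and all interventions were completed by March 29, 2024, aligning with the 12-month study window".
- Trial Design also says that randomization serves "to determine the staggered initiation order of interventions across 4 labor and delivery units", and that "The study involves 4 parallel groups, assigned in a 1:1 ratio, each receiving 1 of 4 interventions".

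On how the orders were generated, Randomization and Allocation says only that this was done "using a computer-generated random number list to determine the sequence of interventions across the 4 LDUs". Figure 1, the study flowchart, is not available in the text reviewed here.

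The Statistical Analysis section names ANOVA or Kruskal-Wallis tests, and t tests between groups. It mentions no term for LDU or calendar period.

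**The concern.** In a stepped wedge, clusters begin in control and cross one way to the intervention at different, randomized times. The schedule described here does neither. Every LDU passes through every condition, control can come in any quarter, and the switches happen on common dates.

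The label matters because it tells the reader which analysis and which variance formula to expect. In a multi-period crossover of clusters, the comparison of conditions is fair over time only if each condition is spread evenly over the calendar periods or if period is adjusted for. The article commits to neither. With tests that ignore LDU and period, any change in VAS scores over the year (case mix, staffing, season, growing familiarity with the techniques) would enter the treatment comparison to the extent that conditions fall unevenly across quarters.

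There is a second consequence. Control can follow an active quarter in the same LDU, where midwives were trained in all three techniques before the start. A standard stepped wedge does not allow that order.

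**Working it through.** **1. Schedule.** Inputs: 4 conditions per LDU (abstract), 3 months each and a 12-month window (Trial Design).

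- Time needed per LDU: 4 × 3 = 12 months, so the slack is 12 − 12 = 0 months.
- If each LDU started one 3-month step after the previous one and still delivered all four conditions: (4 + 3) × 3 = 21 months.

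So all four LDUs must start in month 1 and change condition at the same three dates.

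**2. The plan's own design effect.** Sample Size cites a stepped-wedge method and gives 2.16 with ICC 0.01 and 117 per group. This reproduces as 1 + (117 − 1) × 0.01 = 2.16, the parallel-cluster formula, with no period or step structure. For illustration only, take a Latin square with 147/4 = 36.75 women per LDU-period and an assumed correlation of 0.8 between periods of the same LDU. The crossover form is then 1 + 35.75 × 0.01 − 36.75 × 0.008 = 1.06. Matching the formula to the design therefore need not raise the sample size.

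**3. How uneven could the calendar spread be?** The article does not say how orders were constrained. Suppose, as an assumption, that the four LDU orders were independent random permutations:

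- Chance of a Latin square: 576/24⁴ = 576/331,776 = 0.17%.
- The mean calendar period of combination and control differs in about 89% of draws, and by at least one full quarter in about 35%. The SD of the gap is 0.91 quarters.
- With drift of 0.1 to 0.2 VAS points per quarter, a one-SD gap gives a bias of 0.91 × 0.1 = 0.09 to 0.91 × 0.2 = 0.18 points, against a target difference of 0.7.

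**4. Effect on the named tests.** Simulation with no treatment effect, 37 women per LDU-period, ICC 0.01, between-period correlation 0.8 and two-sided 5% tests. The article gives no SD. The lower value, 1.38, is the one implied by 132 per group if 0.7 is a raw difference: 132/2.16 = 61.1, and 0.7 × √(61.1/2)/(1.960 + 0.842) = 1.38.

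| Orders | Drift per quarter | SD | ANOVA, four groups | t test, combination vs control |
|---|---|---|---|---|
| Independent | 0.2 | 1.38 | about 35% | about 22% |
| Independent | 0.2 | 2.0 | about 19% | about 14% |
| Independent | 0.2 | 2.5 | about 14% | about 10% |
| Independent | 0.1 | 1.38 | about 12% | about 10% |
| Independent | 0.1 | 2.5 | about 8% | about 6% |
| Latin square | 0.1–0.2 | 1.38–2.5 | about 5–6% | about 5–6% |

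Repeat runs differ by one or two percentage points.

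**5. Cost of adjusting.** There are 16 LDU-periods. With LDU, period and condition each taking 3 degrees of freedom, 15 − 9 = 6 remain at the LDU-period level. Under independent orders, the adjusted combination-versus-control contrast has a median efficiency of about 75% of the Latin-square value and is not estimable in about 4% of draws.

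**The case against.** The strongest reply is that the confounding rests on silence. A reader might infer that the sequences were drawn without restriction and that the arms are therefore confounded with time. The article does not say so. A random number list could equally have assigned a balanced set of four sequences to the four LDUs. The sentence about four parallel groups in a 1:1 ratio is most easily reconciled with the schedule if all four conditions run side by side in each quarter, which would be a Latin square. Figure 1 may show the allocation, and an article commonly leaves such a constraint to the full protocol. All of this stands: period confounding is a possibility that the realized allocation will settle, not something the text shows.

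Three other inferences also go too far:

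- *Nothing at all is staggered.* If orders differ between LDUs, a given intervention does begin at different times in different LDUs. Only a stepped-wedge rollout is excluded.
- *The label produced the wrong sample-size formula and the wrong tests.* The stated design effect is the parallel-cluster one, and a stepped-wedge analysis would normally adjust for period. Both are mismatches with the design, but neither follows from the label.
- *Control periods were contaminated.* Prior training of all midwives makes it possible. The article also provides audits, checklists and recording of deviations, and gives no figure from which a dilution could be computed.

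None of this rescues the label. No allocation that the figure could show would fit a stepped-wedge rollout with four 3-month conditions per LDU into 12 months.

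**Conclusion.** The contradiction between label and schedule is established from the article alone. What is described is a 4-period, 4-LDU cluster crossover. The reason given for choosing a stepped wedge, that every group eventually receives the intervention, is met by a crossover too, so nothing is lost by naming it correctly.

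The bias is conditional. If the realized sequences form a Latin square, the named tests keep close to their nominal level and the calendar concern largely disappears. If they do not, the false-positive rate is about 8–35% for the four-group ANOVA and about 6–22% for the combination-versus-control t test. Those ranges assume independent orders, drift of 0.1 to 0.2 VAS points per quarter, SD 1.38 to 2.5 and a between-period correlation of 0.8, none of which the article states; only the ICC of 0.01 is its own. If all LDUs happened to follow one common order, condition and quarter would coincide completely and no adjustment could separate them.

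**What to change.** 1. Call the trial a 4-period, 4-LDU cluster crossover in the title, Trial Design and Sample Size text. Remove or reword the stepped-wedge and parallel-group descriptions, and use a design effect that matches, with its between-period correlation stated as an assumption.
2. Report the realized allocation of conditions to LDUs and quarters, with the number of women in each cell, and say whether the sequences were constrained to balance over periods.
3. Make the combination-versus-control contrast adjusted for LDU and period the primary estimate. The named unadjusted tests can remain as descriptive support. Record the change before group results are examined; the Results section says that analysis is in progress.
4. Use the existing adherence logs to describe how often active techniques were used in control periods. Excluding women recruited just after each switch is optional; nothing in the article requires it.

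The cost is wording, one table and a modest amount of analysis. Adjustment uses degrees of freedom and, if the sequences are unbalanced, loses some precision. No new data are needed.
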